## Study procedures

Available clinical information will be collected from all patients both at inclusion and at follow-up. After inclusion, we will aim to investigate all patients in the outpatient clinic of the Department of Neurology, LUMC. In our experience, some patients with both SCLC and LEMS will not be able or willing to visit the LUMC because of their physical condition, especially after starting chemo- and radiotherapy. In order to maximize participation, we will still ask their consent for obtaining medical correspondence and for a researcher to visit and see them in their local hospital.

### Blood sample

Each patient will be asked to donate blood. It will concur with the regular blood sample drawn at diagnosis.

We will draw 90 ml of blood additionally:

-70 ml to isolate serum, test for antibodies and peripheral blood mononuclear cells

-20 ml to isolate and store DNA

For patients with SCLC, we will draw up to 50 ml of blood a second time at follow-up for immunophenotyping.

The samples will be handled in Leiden to extract DNA (Laboratory for Diagnostic Genome Analysis, prof.dr. [name]), to obtain serum and to isolate cells that will be frozen and stored (laboratory of Clinical Oncology, prof. dr. [name]).

### Electromyography

Patients with clinical signs or symptoms of LEMS will all be seen by a neurologist from the LUMC. They will be asked to have an electromyographical study (EMG). This forms a very sensitive test for LEMS. For LEMS the amplitude of the compound muscle action potential (CMAP) and the amount of decrement or increment will be determined by repetitive nerve stimulation and registration from the abductor digiti minimi, nasalis and trapezius muscles. This investigation is part of regular care for patients with LEMS.

### Imaging studies

For patients with SCLC we will ask for permission to collect their previous lung imaging studies. This will allow us to compare size and distribution of the lung tumour for patients with and without LEMS. As for tumour tissue, we have collected clinical data of multiple SCLC-LEMS patients. For the same reasons stated in the previous paragraph, we will not obtain specific permission for obtaining imaging studies of patients who are already deceased. Instead we will request these imaging studies directly, stating this procedure is supported by the METC.

### Analysis of humoral and cellular immune response

*Mechanism of tumour immune response*

Tumour infiltration by lymphocytes and macrophages has been investigated in detail in several types of cancer including SCLC and seems to be associated with survival advantage.^15, 17, 37^ SCLC is a very immunogenic tumour, leading to more frequent occurrence of paraneoplastic syndromes compared to other tumours.^5^ The prolonged tumour survival associated with some of these paraneoplastic syndromes suggests a functional immune response against both tumour and healthy tissue. However, the pathways by which the immune system can control tumour growth remain unclear. The frequent occurrence of onconeuronal antibodies without the corresponding clinical syndrome is not related to a survival advantage in SCLC patients, suggesting that the antibody response is required but not sufficient to cause the clinical syndrome, including an effective anti-tumour response.^11, 38^ We will study multiple possible pathways that could lead to a more tumour-rejecting type of immune response. Also, we will search for other contributing immune responses, e.g. tumour infiltration, that can influence prognosis in SCLC patients.

*a). What type of macrophages are present in LEMS+ SCLC?*

Tumour-promoting M2 type macrophages are identified via their expression of CD163. Recently we showed that these cells can be easily identified via staining for CD68 (all types of macrophages) and the absence (M1 type) or presence (M2 type) of CD163.^34^

We will stain SCLC tumour sections from patients with and without LEMS and VGCC antibodies for different antigen-presenting cell markers and quantify these cells per square mm tumour. Quantification can be automatically done.^34^ This will allow us to assess what type of function the macrophages may have within the tumours of LEMS+ patients.

We will also determine whether predominance of a macrophage subtype can predict survival in all SCLC patients.

*b). Tumour-infiltrating lymphocytes*

To assess if lymphocyte infiltration (especially B-cells) of SCLC is related to better survival for SCLC patients with Hu, SOX and VGCC antibodies and SCLC patients without PNS, we will stain tumour sections for CD20 (B cells), and CD3 (T cells) to quantify and determine their relation with disease-free and overall survival. If T cells play a role we will stain a number of tumours for CD8, CD4 and Foxp3 in order to gain more information about the type of T cell infiltrate (CD8; cytotoxic T cells, CD4; T-helper cells, CD4+Foxp3+; regulatory T cells).

*c). Do VGCC antibodies mediate an anti-tumour effect?*

High titres of VGCC-specific IgG antibodies are readily detected in the serum of patients. There are a number of SCLC cell lines available (e.g. NCI-H146, NCI-H345), which display functionally active P/Q type of VGCC.^39^ Microscopy studies suggest that VGCCs are desorganized and become clustered on the cells of LEMS patients resulting in lowered signalling function, however this would allow VGCC-specific antibodies to bind more easily and to function as targets for activated macrophages.^40^

- To assess whether VGCC-antibodies can kill tumour cells via complement binding, we will incubate P/Q type VGCC positive and negative SCLC with serum of VGCC+-SCLC patients and study direct tumour kill.^41, 42^ As a control we will also use serum of VGCC- SCLC patients, as well as heat-inactivated serum to show the effect is complement-mediated.

- To assess whether VGCC-specific antibodies can induce antibody dependent cellular cytotoxicity we will incubate the cell lines with patient-derived serum, add activated M1 or M2 macrophages and study tumour kill.^41, 43^

*d). Can VGCC antibodies stimulate the adaptive anti-tumour response?*

Recently we showed that the binding of antibodies to tumour cells can directly influence the local tumour environment by binding to the Fc-receptors present at the surface of macrophages which – through their fixed state on tumour cells – will result in the activation of the macrophage. Dependent on the abundance of the type of macrophage this may result in a tumour-rejecting or tumour-promoting environment.^36^ Based on the expression of the P/Q-type VGCC at the surface of tumour cells, bound VGCC antibodies are also likely to induce macrophage activation.

We will add VGCC Ab+ and VGCC Ab- serum to tumour cell lines and incubate them with in vitro produced M1 and M2 macrophages as well as dendritic cells (DC). The macrophages and DC will be studied for the typical surface markers associated with activation, as well as for the production of cytokines associated with tumour-rejection (IL12p70) or tumour-promotion (IL-10, IL-6).

*e). Do SCLC patients display specific CD4+ T-cells against tumour-related antigens?*

The presence of VGCC, Hu and SOX IgG antibodies indicate that T-helper dependent antibody isotype switching has occurred, and as a consequence that patients would have mounted an antigen-specific CD4+ T cell response. While such an auto-immune response is likely to be controlled by regulatory T cells (Tregs), patients with PNS, including LEMS, show lower levels of Tregs. We have produced recombinant proteins of the different VGCC sub-units. BMC isolated from LEMS+ and LEMS- patients with SCLC will be stimulated with autologous recombinant protein pulsed monocytes and tested by proliferation assays, cytokine ELISA and multiparameter flow cytometry in order to determine the presence, specificity and type of VGCC-specific T cells as described before by us.^44^

*f). Do VGCC antibodies lead to improved tumour-immunity via opsonization of tumour antigens?*

SCLC tumour cells expressing P/Q-type VGCC will be incubated with or without VGCC antibodies (or VGCC-Ab+patient serum) and co-cultured with monocyte-derived M1 macrophages or dendritic cells from patients’ peripheral blood mononuclear cells (PBMC). Autologous (patient-derived) PBMC will be added and the difference in stimulation of T cells will be followed through the expression of early and late activation markers as well as the production of cytokines.

*g). Do SCLC patients with and without LEMS differ in cellular immune response?*

We will study peripheral blood mononuclear cells using immunophenotyping by flow cytometry. We will compare LEMS+, LEMS- SCLC patients and LEMS patients without associated tumour. In SCLC patients, we will ask patients to donate blood upon follow-up as well, concurring with a regular blood sample. This will allow us to study the cellular immune response before and after chemotherapy.

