# OBJECTIVES

*Main objective:*

To understand the pathophysiology of the immune response against VGCC in tumour- and non-tumour related LEMS.

*Specific objectives:*

1. To describe in detail the epidemiology, clinical characteristics (including imaging studies) and disease course of the Lambert-Eaton myasthenic syndrome with or without SCLC.
2. To prospectively test the ability of the DELTA-P score to predict the presence of an underlying SCLC in LEMS patients.
3. To study biomarkers in the peripheral blood of patients with LEMS, LEMS and SCLC, or SCLC only.
4. To study the humoral and cellular aspects of the tumour immune response in patients with SCLC and LEMS.

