# METHODS

## Study parameters/endpoints

Parameters/endpoints for each of the objectives stated in chapter 3:

1. Epidemiology, clinical characteristics and disease course of LEMS with/without SCLC

*Introduction*

Many of our previous studies have focussed on clinical characteristics of LEMS patients. Based on the previous years, we expect to include 4-6 LEMS patients per year. For most clinical characteristics and the disease course, we will not define specific endpoints in advance.

We will specifically focus on lung imaging studies to determine tumour size and growth upon diagnosis in SCLC-LEMS patients compared to SCLC only. A prolonged survival has been observed in SCLC-LEMS patients, as well as increased tumour infiltration by macrophages.^16^ Lung tumours in LEMS are also frequently present in mediastinal lymph nodes only. Imaging studies in these patients might therefore show a difference in tumour size and growth as well as distribution.

*Hypothesis*

Lung tumours in SCLC-LEMS patients are smaller on average and grow at a slower rate compared to tumours in SCLC patients without LEMS.

*Endpoints*

Tumour size and growth rate upon follow-up.

Distribution of metastases.

1. To prospectively test the ability of the DELTA-P score to predict the presence of an underlying SCLC in LEMS patients.

*Introduction*

Detailed analysis of clinical and demographic characteristics from two independent patient cohorts has led us to develop the DELTA-P score.^25^ This prediction model has provided for a simple clinical tool to indicate the presence of SCLC early in the course of the disease and can be used to guide tumour screening in individual patients. This model has not yet been investigated prospectively.

*Hypothesis*

The DELTA-P score accurately predicts presence of SCLC in newly diagnosed LEMS patients.

*Endpoints*

Clinical characteristics necessary for DELTA-P score.

Diagnosis of SCLC upon follow-up.

1. Biomarkers in the peripheral blood of patients with LEMS, SCLC-LEMS, or SCLC only.

*Introduction*

Multiple biomarkers for LEMS have been studied in our cohort. We have previously identified SOX antibodies as specific serological marker for SCLC-LEMS.^24, 33^ Antibodies against the intracellular Hu protein are also found in SCLC patients with and without LEMS. Additionally, HLA-B8-DR3 was identified as a biomarker for LEMS without associated tumour.^14, 27^

*Hypothesis*

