Multiple biomarkers including auto-antibodies and HLA type are present in LEMS and are associated with specific disease subgroups.

*Parameters*

We will test for Hu and SOX antibodies as well as HLA type.

*Future objectives:*

It is likely that in the future other biomarkers will become available. Currently, we are collaborating with prof. dr. [name] and dr. [name] (Dept. of Human Genetics) to search for new biomarkers. We expect that our study will identify patients with prolonged tumour survival or a favourable anti-tumour immune response. For these patients, genetic polymorphisms will be valuable for our understanding of the immune mechanism. The unfortunate poor survival of this patient group makes it impossible to ask for DNA samples to be taken later on during the study. Thus, because of the nature of this prospective study, combining detailed clinical and immunological data, we will store DNA for analysis in future studies.

1. Humoral and cellular aspects of the tumour immune response in SCLC-LEMS

*Introduction*

SCLC is a very immunogenic tumour, leading to more frequent occurrence of paraneoplastic syndromes compared to other tumours.^5^ The prolonged tumour survival associated with some of these paraneoplastic syndromes suggests a functional immune response against both tumour and healthy tissue. However, the pathways by which the immune system can control tumour growth remain unclear. We will study multiple possible pathways that could lead to a more tumour-rejecting type of immune response.

*Hypothesis*

- SCLC biopsies in LEMS patients show an increase in tumour infiltration by lymphocytes and macrophages.
- An anti-tumour effect of serum VGCC antibodies and related cellular immune responses can be detected *in vitro*.
- Specific T cells against tumour-related antigens, such as VGCC, are present in serum of LEMS patients.

*Parameters*

- Tumour infiltration of SCLC by lymphocytes and macrophages (+- LEMS)
- Anti-tumour effect of serum VGCC antibodies and related macrophage and adaptive response in vitro
- Presence of specific T cells against tumour-related antigens

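### The only VGCC-specific T-cell assay takes no cells from LEMS patients without tumour, so it cannot serve the non-tumour half of the main objective for that response

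*Combined protocol and SAP*

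**What the plan says.** All references are to the Dutch protocol within the combined document.

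Section 2 gives the main objective as "To understand the pathophysiology of the immune response against VGCC in tumour- and non-tumour related LEMS". Specific objective 4, which the laboratory work in 5.2.5 serves, is narrower: "To study the humoral and cellular aspects of the tumour immune response in patients with SCLC and LEMS". Under objective 4, section 5.1 states this hypothesis: "Specific T cells against tumour-related antigens, such as VGCC, are present in serum of LEMS patients". It is not restricted to patients with a tumour.

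Section 5.2.5 e, the assay that tests this hypothesis, describes its donors as follows: "BMC isolated from LEMS+ and LEMS- patients with SCLC will be stimulated with autologous recombinant protein pulsed monocytes".

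The complement part of 5.2.5 c reads "we will incubate P/Q type VGCC positive and negative SCLC with serum of VGCC+-SCLC patients and study direct tumour kill", with these controls: "As a control we will also use serum of VGCC- SCLC patients, as well as heat-inactivated serum to show the effect is complement-mediated".

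On other antibodies, section 5.1 (objective 3) says "We have previously identified SOX antibodies as specific serological marker for SCLC-LEMS". It describes Hu as an intracellular protein whose antibodies occur in SCLC both with and without LEMS. Hu antibodies, SOX antibodies and HLA type are all to be tested. Section 5.2.1 asks every patient for 70 ml for serum, antibody tests and mononuclear cells.

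**The concern.** The protocol's own reasoning makes tumour versus non-tumour LEMS a central contrast. The introduction reports that non-tumour LEMS is strongly tied to one HLA haplotype while SCLC-LEMS is not, and takes this to suggest that the tumour itself starts the autoimmune reaction. A T-cell response to VGCC is a direct place to examine that idea. If the response is measured only in people with SCLC, a positive finding in SCLC-LEMS has two readings: the tumour drives it, or it belongs to LEMS whatever the cause. The assay as written cannot choose between them.

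A second, smaller issue concerns the complement-kill assay. Serum from VGCC-positive SCLC patients may differ from VGCC-negative SCLC serum in more than the VGCC antibody. If another tumour-induced antibody does the killing, part of the effect could be credited to the wrong antibody.

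**Working it through.** The plan gives no sample size, error rate or effect size for any immunological endpoint; section 6 names only the database and software. There is no figure of the plan's to reproduce. The check is a mapping of assays to donors, plus one piece of arithmetic.

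**Step 1. Who supplies each blood-based assay in 5.2.5**

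| Part | Donors named | Measures a VGCC-specific T-cell response? |
|---|---|---|
| c, complement kill | VGCC-positive SCLC; VGCC-negative SCLC as control | No |
| c, cell-mediated kill | Patient serum, group not stated | No |
| d, macrophage and dendritic-cell activation | VGCC antibody-positive and -negative serum, tumour status not stated | No |
| e, recombinant VGCC stimulation | SCLC with LEMS; SCLC without LEMS | Yes |
| f, opsonisation | Patients' mononuclear cells, group not stated | No; T-cell stimulation is read out, but the stimulus is whole tumour cells |
| g, immunophenotyping | SCLC with LEMS, SCLC without LEMS, LEMS without tumour | No |

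Tumour-free LEMS is named only in (g). Objective 3 adds Hu, SOX and HLA, none of which is a T-cell response to VGCC. The UK protocol in the same document stores whole blood and serum for antibody work and plans no T-cell assay, so it does not fill the gap.

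**Step 2. What (e) can identify**

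Cross-classify donors by tumour (yes/no) and LEMS (yes/no). Assay (e) fills two of the four cells, both with tumour present. Their difference shows what LEMS adds among people with SCLC. What the tumour adds among people with LEMS is SCLC-LEMS minus LEMS without tumour, and the second term is not measured.

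**Step 3. How many donors are left out**

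Inputs: 4-6 LEMS patients a year (section 5.1, objective 1) and 50-60% of LEMS with SCLC (section 1).

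- Tumour-free LEMS per year = accrual × (1 − SCLC share). Low: 4 × (1 − 0.60) = 1.6. High: 6 × (1 − 0.50) = 3.0.
- SCLC-LEMS per year = accrual × SCLC share. Low: 4 × 0.50 = 2.0. High: 6 × 0.60 = 3.6.
- Share of the LEMS cohort outside (e): 1 − 0.60 = 40% to 1 − 0.50 = 50%.

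**Step 4. What the complement assay controls**

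- Heat-inactivated serum tests whether killing needs complement. It does not say which antibody acts.
- VGCC-negative SCLC serum removes effects common to SCLC serum.
- VGCC-negative cells remove effects of antibodies to antigens shared by both kinds of target cell.

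What remains is an antibody that accompanies the VGCC antibody and binds an antigen found on the VGCC-positive cells but not on the VGCC-negative ones. The protocol does not say that the lines are alike apart from VGCC. SOX is a candidate because the protocol ties it to SCLC-LEMS. Hu is a weaker one, being described as intracellular and as present with and without LEMS. Part (d) uses whole serum too and does not list a VGCC-negative line.

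**The case against.** The best defence is that 5.2.5 was built for objective 4, which concerns the tumour immune response in SCLC with LEMS, and that the heading of (e) asks about SCLC patients. For that question, and for the summary's interest in prolonged survival, SCLC with LEMS against SCLC without LEMS is the right contrast. This stands, and the contrast should be kept. It does not close the gap: the hypothesis under objective 4 speaks of LEMS patients without restriction, and if (e) is read narrowly, no other assay measures VGCC-specific T cells in non-tumour LEMS.

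A reader might go further and infer that the main objective cannot be answered at all. The documents do not support that. Antibodies and HLA type are compared across the LEMS groups, (g) includes tumour-free LEMS, and the cell-mediated part of (c), together with (d) and (f), does not exclude their samples.

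A reader might also infer that tumour kill cannot be attributed to VGCC antibodies. That is too strong as well. The complement assay has an antigen-negative target, an antibody-negative serum and a heat-inactivated control. Part (f) allows VGCC antibodies in place of whole serum. SOX and Hu status will be known.

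**Conclusion.** The point holds for VGCC-specific T cells. The main objective and the T-cell hypothesis include LEMS without tumour, the single assay of that response does not, and 40-50% of the LEMS cohort (about 1.6-3.0 patients a year) is outside it. For the complement-kill assay the conclusion is weaker: attribution is partly controlled, and confounding by SOX or another tumour-induced antibody is possible rather than shown.

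It would be tempting to rule that VGCC antibodies act only if tumour-free LEMS serum also kills, and that otherwise the tumour immune response is responsible. The two are not alternatives, since section 1 holds it likely that the tumour itself triggers the autoantibodies. A negative result could also reflect a different titre or the small number of sera.

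The counts assume that the protocol's accrual and SCLC share apply to the patients who give blood, and that each draw yields enough cells. The documents give no cell yields. This should be changed, but it does not undermine the rest of the laboratory programme.

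**What to change.** - In 5.2.5 e, run the recombinant-VGCC assay in three groups: SCLC-LEMS, LEMS without tumour, and SCLC without LEMS. Use the mononuclear cells already collected. Assign tumour status after the follow-up defined in section 8.4, because blood is drawn at diagnosis and a tumour may be found later.
- In 5.2.5 c, add VGCC-positive serum from tumour-free LEMS patients as a further arm. In (d), include the VGCC-negative line as well.
- State the serum donor group in the cell-mediated part of (c), in (d) and in (f).
- Report SOX and Hu status for each serum used; both are already being tested.
- State in advance that the tumour-free serum result is supporting evidence, with the number of sera shown.

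The cost is extra assay runs and the use of stored cells and serum from tumour-free LEMS patients. No new patients, visits or procedures are needed. The 70 ml must serve several assays, so the order of priority for scarce cells should be written down. If the cells do not suffice for (e), the alternative is to limit the main objective, for VGCC-specific T cells, to SCLC-LEMS.

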## Withdrawal of individual subjects

Subjects can leave the study at any time for any reason if they wish to do so without any consequences. The investigator can decide to withdraw a subject from the study for urgent medical reasons.

# STATISTICAL ANALYSIS

We will establish a database (MS Access) for clinical characteristics and lab results. Statistical analysis will be carried out by SPSS (SPSS 20.0, Chicago, IL, USA) and / or GraphPad Prism 5.01 (GraphPad Software Inc, La Jolla, CA, USA).

# ETHICAL CONSIDERATIONS

## Regulation statement

The study will be conducted in compliance with the protocol, the ethical principles that have their origin in the Declaration of Helsinki (Version 9, amended by the 59^th^ WMA general Assembly, Seoul, October 2008) and in accordance with the Medical Research Involving Human Subjects Act (WMO).

